## Assignment of interventions: allocation

### Sequence generation {16a}

A total of 40 patients will be recruited. After an eligibility assessment and informed consent, participants will be assigned to the experimental arm or control arm with allocation ratio 1:1. The randomisation sequence and grouping will be generated by one researcher who will not be involved directly in patient screening, enrolment or assessment, and uploaded to Research Electronic Data Capture (REDCap) [16, 17]. No stratification will be utilised. The randomisation tables were set up using permuted blocks with random varying block sizes of 4 and 6.

### Concealment mechanism {16b}

The BRAVEHeart trial uses allocation concealment with patients randomly assigned to each treatment arm in REDcap as described above in the “Sequence generation {16a}” section. As the trial is to use one device versus another, the arm a patient is assigned to cannot be concealed to the patient or the treatment team.

### Implementation {16c}

Randomisation is performed at the site electronically by the hospital clinical trials staff using REDCap. The allocation sequence is locked down within the REDCap database and is not accessible to anyone.

## Assignment of interventions: blinding

### Who will be blinded {17a}

No blinding will be used in this trial.

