Breathe Well (Fig. 1) is a new audiovisual (AV) feedback device developed at the University of Sydney that may increase the efficacy and improve the workflow of implementing DIBH for breast cancer patients. Breathe Well is clamped on the superior end of the computed tomography (CT) couch or treatment couch and uses depth and optical sensors to directly monitor a user-defined area on a patient’s chest. The positional accuracy and precision of the depth sensor has been shown to be within ± 1.0 mm and the temporal stability of the sensor is sub-mm [12]. The horizontal and vertical axes of the device can be adjusted to fit the patient and immobilisation device dimensions and the device arm can be rotated to enable an unobstructed patient setup and an optimal view of the included screen when the patients are treated with their head tilted (Fig. 1A). The monitoring region of interest is selected by the radiation therapist from within the optical field of view e.g. centred on the sternal tattoo and corresponds to an area of a few square centimetres on the patient’s chest. Within the Breathe Well software application a patient-specific reference breath hold with respect to the normal breathing baseline can be measured and stored. The included screen delivers real-time feedback to the patient regarding their chest position. The breath hold target area (gating window) is highlighted and depending on the workflow status the screen (Fig. 1B) shows an orange wait screen or instructs the patient to hold their breath or relax. An optional breath hold countdown option helps the patient to see how long they still have to hold their breath. At their workstation, the radiation therapists also see the real-time visual feedback indicating when the breath hold depth is acceptable, allowing them to control treatment delivery.

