### Intervention description {11a}

Training and simulation: The patients will be trained to perform DIBH with the assigned system and assessed for ability to perform a 20-s breath hold (at 80–90% of the maximal lung capacity). Based on this screening the patient will be deemed suitable for DIBH. For patients suitable for DIBH the breath hold AV guidance while acquiring the planning CT scan will be provided by the assigned system. The unallocated system will be set up to passively record motion. The RPM/RGSC marker block is not within the field of view of the Breathe Well camera, and the Breathe Well device does not interfere with RPM/RGSC tracking the marker block. The reference breath hold depth will be recorded for both systems.

Treatment delivery: For treatment, similarly to simulation, both systems will be set up to monitor breathing motion. The patient will be guided with AV biofeedback from the assigned system depending which arm of the trial they have been randomised to. The unallocated system will passively acquire data but not interfere with treatment in any way. Prior tests showed that no interferences and difficulties are anticipated when operating the ‘Breathe Well’ system and the RPM/RGSC system at the same time. If any treatment fraction cannot be delivered due to a failure of the Breathe Well device, this will be recorded. The treatment will continue at the physician’s discretion either (1) using the RPM system, (2) the fraction will be rescheduled or (3) delivered using free breathing.

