### Outcomes {12}

Primary outcome:

Treatment accuracy: the specific measurement made will be the average chest wall position extracted from the EPID images captured at each treatment fraction. The metric used for analysis will be the ‘displacement’ or difference between this measured position on each captured image frame and the planned average chest wall position from the digitally reconstructed radiograph (DRR). The average per fraction displacements will be compared across the two arms of the trial.

Secondary outcomes:Setup time: The appointment duration will be measured as the time recorded in the ARIA patient management system between patient check-in and appointment end for each treatment fraction, and aggregated for each arm of the trial.Patient comfort and user friendliness. A patient survey (see Supplementary Materials) will be delivered at the timepoints indicated in the “Participant timeline {13}” section and Fig. 3: after simulation, and at the end of the first and last weeks of treatment.Technology assessment: A staff survey (see Supplementary Materials) will be delivered at the timepoints indicated in Fig. 3: after 5 and 10 sessions using Breathe Well at CT simulation and after 5 and 20 sessions using Breathe Well at treatment.To develop — offline — the use of the electronic portal imaging device (EPID) for real-time MLC tracking during monitoring the chest wall position in breast radiotherapy. This work will be reported as future research outputs.Estimated dose delivered. Measured chest wall displacement relative to planned position (taken from the EPID images captured at treatment time, see the primary outcome) will be used to apply an isocentre shift in the treatment planning system, following the approach of Doebrich et al. [13]. Hence the delivered dose will be estimated for each patient during each treatment fraction and aggregated for each arm of the trial.

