### Data management {19}

Respiratory data (‘Breathe Well’ and RPM/RGSC), CT images, MV frames from during the irradiation, and demographic information will be collected from the subjects. At the randomisation stage of the study, patients will receive a trial ID. The data saved for the trial will be under this de-identified trial ID. A separate key of the subject study number and their medical record number will be securely stored by the chief investigator to allow re-identification if necessary. This master list for re-identification will remain at the Royal North Shore Hospital. Only the principal investigator will have the ability to re-identify subjects. Questionnaire and toxicity information will be entered in REDCap and collated information transferred to the same secure drive at the University of Sydney for storage. The data will be stored for 15 years as per clinical trial guidelines. Data sent from the Northern Sydney Cancer Centre, Royal North Shore Hospital in accordance with the study site’s ethics and security allowances and protocols to the study site University of Sydney will be anonymised but re-identifiable. Patient data could be made re-identifiable to obtain additional clinical information for the data analysis stage of the project, but only by the principal investigator. The de-identified data will be stored at the University of Sydney on a secure, password-protected backed-up database that will be created, much the same as what we have designed for previous University of Sydney studies.

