### Confidentiality {27}

At the hospital, copies of questionnaires will be stored in a locked cabinet. Digital information will be stored on the secure local network. Data will be anonymised before leaving the hospital and being transferred to the University of Sydney for storage on a secure, password-protected drive accessible by authorised researchers only. The anonymisation table will remain at Royal North Shore Hospital.

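### Blinding is ruled out for everyone, but the stated reason covers only patients and treatment staff; those who read the EPID images and reconstruct dose could be masked to arm at low cost

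*Protocol article*

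**What the plan says.** Section {17a} states: "No blinding will be used in this trial". No exception is made for outcome assessment. The nearest thing to a justification is in {16b}: because one device is compared with another, "the arm a patient is assigned to cannot be concealed to the patient or the treatment team".

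For the primary outcome, {12} says that "the specific measurement made will be the average chest wall position extracted from the EPID images captured at each treatment fraction". Displacement is the difference between that position on each frame and the planned position on the digitally reconstructed radiograph. The same displacements feed the estimated delivered dose, a secondary outcome.

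On how sessions run, {11a} has both systems set up at simulation and at treatment, and adds: "The unallocated system will passively acquire data but not interfere with treatment in any way".

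On data handling, {19} lists "MV frames from during the irradiation" among the data collected and says: "The data saved for the trial will be under this de-identified trial ID". Section {27} adds: "Data will be anonymised before leaving the hospital". The de-identified data are then held at the University of Sydney. Section {6a} describes Breathe Well as a "new audiovisual (AV) feedback device developed at the University of Sydney".

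**The concern.** A trial in which patients and therapists must know the arm can still have its outcome read by someone who does not. Here the plan states the opposite as a rule. This is not detail left to an analysis plan, because an analysis plan that masked the readers would contradict {17a}.

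At stake is the credibility of the primary comparison. The hypothesis is that Breathe Well is superior, and the data are held at the institution that developed it. If extracting the chest wall, discarding a frame or correcting a reading involves judgement, knowledge of the arm can influence it. Any such influence would carry over to the dose outcome, which reuses the displacements and is formally tested only if the primary result favours Breathe Well.

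**Working it through.** The plan gives no figure on this point, so the main check sets its statements side by side.

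1. **Scope of the rule and scope of the reason.** The rule in {17a} covers everyone. The reason in {16b} covers two groups, patients and the treatment team. Image readers and dose reconstruction staff fall under the rule but not under the reason.
2. **Can the outcome be read away from the treatment room?** The frames are collected as trial data ({12}, {19}), so reading them after the session is a fair inference. It is not stated: the protocol uses the word offline only for the MLC-tracking objective.
3. **Would the images show the arm?** Both systems are present in both arms ({11a}), and {6a} says the RPM/RGSC marker block is usually positioned outside the treatment field. Equipment in view therefore need not give the arm away. Delivery does differ. RPM/RGSC gates the beam automatically, while with Breathe Well the therapists act on what they see ({6a}). A fraction affected by Breathe Well failure may be given with RPM or in free breathing ({11a}). Frame patterns could sometimes hint at the arm.
4. **Is the trial ID already a mask?** No. It hides the patient's identity. It hides the arm only if the allocation is also withheld from the reader, and nothing in the document provides for that.

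**Illustration only.** The document gives no size for a reading bias. The table assumes one, to show how far the answer depends on its form. Inputs from {14}: Σ = 1.33 mm (RPM) or 0.46 mm (surface system), and 36 evaluable patients, hence 18 per arm. Assumed: equal true accuracy, zero-mean normal errors, no random error component, and a shift b in one arm in the direction that favours Breathe Well.

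- SD of absolute displacement = Σ√(1 − 2/π) = 1.33 × 0.603 = 0.802 mm
- SE of the difference = 0.802 × √(2/18) = 0.267 mm
- Probability of false superiority at one-sided 5% = 1 − Φ(1.645 − b/SE)
- For b = 0.1: b/SE = 0.37, P(Z > 1.27) = 0.10. For b = 0.2: b/SE = 0.75, P(Z > 0.90) = 0.185
- If instead every read position moves by a constant b, mean absolute displacement changes by only about b²/(Σ√(2π)): 0.01/3.33 = 0.003 mm, or 0.04/3.33 = 0.012 mm

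| What is assumed to shift, and test | SE (mm) | b = 0.1 mm | b = 0.2 mm |
|---|---|---|---|
| Mean absolute displacement, Σ 1.33, one-sided 5% | 0.267 | 10% | 19% |
| Same, favourable tail of a two-sided 5% test (nominal 2.5%) | 0.267 | 5.6% | 11.3% |
| Mean absolute displacement, Σ 0.46 in both arms, one-sided 5% | 0.092 | 29% | 70% |
| Mean signed displacement, Σ 1.33, one-sided 5% | 0.443 | 7.8% | 11.6% |
| Constant shift in read position, outcome absolute, Σ 1.33, one-sided 5% | 0.267 | 5.1% | 5.5% |

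The range runs from almost nothing to very large. The protocol does not settle which row applies: it states neither whether displacement is absolute nor whether alpha is one- or two-sided. Random error would enlarge the SE and lower the figures.

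**The case against.** The strongest objection is that the mechanism is assumed. Nowhere does the protocol describe manual edge placement, frame selection or correction. Displacement is defined on each captured frame, and extraction may be automatic, in which case knowing the arm could matter very little. This stands, and it limits the expected gain. It does not justify the rule, since the protocol does not say that extraction is automatic.

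Second, masking may be imperfect because beam control differs between arms. This also stands, but an occasional hint is weaker than a known label.

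Third, on the design assumptions the expected difference in mean absolute displacement is √(2/π) × (1.33 − 0.46) = 0.69 mm, well above the shifts of 0.1 and 0.2 mm used in the illustration. So it would be wrong to say that the trial turns on a few tenths of a millimetre.

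Fourth, the primary model is already fixed as a generalised estimating equation with no covariate adjustment, subgroup or sensitivity analysis. That leaves the analyst little room, so the case for masking lies mainly with image reading and the dose work that follows from it.

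**Conclusion.** The point holds in a limited form. Section {17a} rules out all blinding, and the reason given does not cover those who extract chest wall position or reconstruct dose. On the protocol's own description, masking them looks feasible. It would limit one source of bias, the reader's knowledge of the arm. Unblinded delivery and the unblinded patient and staff surveys would be unaffected.

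Three stronger readings are tempting, and the document supports none of them.

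- A reader might infer that measurement is in fact biased towards Breathe Well. Nothing shows this; the developer's role is a reason for care, not evidence of bias.
- A reader might take 10% and 19% as the trial's false-superiority risk. They hold only for a hypothetical shift of 0.1 or 0.2 mm in mean absolute displacement in one arm, under a one-sided 5% test. A constant shift in read position of the same size gives 5.1% and 5.5%.
- A reader might conclude that sessions are identical in the two arms, so that masking would be free and would remove measurement bias. The equipment present is the same but guidance and beam control differ, there is a small cost, and only one source of bias is limited.

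The amendment is worth making because it is cheap and protects the primary outcome, not because a bias of known size has been found.

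**What to change.** Amend {17a} to say that patients and treatment staff are unblinded, while chest wall extraction, any frame exclusion or correction, and dose reconstruction are done on files coded without the arm. Frame exclusions and extracted positions are locked before the allocation is merged. If extraction is fully automatic, say so; the lock step still covers any exclusions or manual corrections.

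The cost is relabelling the files and one lock step. Sample size, visits and care do not change, and no extra reader is needed. Because the frames are stored, masked extraction or re-extraction remains possible after recruitment has ended.

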### Procedure for unblinding if needed {17b}

Not applicable.

## Data collection and management

### Plans for assessment and collection of outcomes {18a}

Collection of data during treatment will be initiated by the radiation therapists delivering the treatment. Clinical trials staff will administer the ease-of-use questionnaires (see Additional file 1) with the results entered in REDCap. Clinicians will administer baseline and toxicity questionnaires, with the results entered in REDCap.

### Plans to promote participant retention and complete follow-up {18b}

Participants are only required to attend treatment and follow-up appointments as normally required for their treatment and no dropout is expected. Clinicians and radiotherapy staff will be trained to answer any participant questions or concerns about the trial.

### Data management {19}

Respiratory data (‘Breathe Well’ and RPM/RGSC), CT images, MV frames from during the irradiation, and demographic information will be collected from the subjects. At the randomisation stage of the study, patients will receive a trial ID. The data saved for the trial will be under this de-identified trial ID. A separate key of the subject study number and their medical record number will be securely stored by the chief investigator to allow re-identification if necessary. This master list for re-identification will remain at the Royal North Shore Hospital. Only the principal investigator will have the ability to re-identify subjects. Questionnaire and toxicity information will be entered in REDCap and collated information transferred to the same secure drive at the University of Sydney for storage. The data will be stored for 15 years as per clinical trial guidelines. Data sent from the Northern Sydney Cancer Centre, Royal North Shore Hospital in accordance with the study site’s ethics and security allowances and protocols to the study site University of Sydney will be anonymised but re-identifiable. Patient data could be made re-identifiable to obtain additional clinical information for the data analysis stage of the project, but only by the principal investigator. The de-identified data will be stored at the University of Sydney on a secure, password-protected backed-up database that will be created, much the same as what we have designed for previous University of Sydney studies.

### Confidentiality {27}

At the hospital, copies of questionnaires will be stored in a locked cabinet. Digital information will be stored on the secure local network. Data will be anonymised before leaving the hospital and being transferred to the University of Sydney for storage on a secure, password-protected drive accessible by authorised researchers only. The anonymisation table will remain at Royal North Shore Hospital.

### Plans for collection, laboratory evaluation and storage of biological specimens for genetic or molecular analysis in this trial/future use {33}

Not applicable.

## Statistical methods

### Statistical methods for primary and secondary outcomes {20a}

Primary outcome:

Treatment accuracy: a generalized estimating equation model with exchangeable correlation structure which adjusts for repeated measurements within individuals will be used to test the per fraction average chest wall displacements for all patients on each arm, testing for superiority (smaller chest wall displacement) of the Breathe Well arm compared to the RPM arm. No covariate adjustment, subgroup or sensitivity analysis is planned.

Secondary outcomes:

1. Setup time: Median and range of the appointment time will be reported for each arm. No statistical analysis is planned as clinically significant variation in the appointment time is highly dependent on hospital procedures and workflow.

2. Patient comfort and user friendliness and 3. Technology assessment: The questionnaire tools used for secondary aims 2 and 3 are not validated tools so will only be used for qualitative analysis. The median and range response scores will be reported for each arm for each question.

5. Estimated dose delivered: If the primary outcome shows superiority of the Breathe Well arm in treatment accuracy, the same model will be used to test for superiority (smaller dose differences) of the dose distributions between the Breathe Well arm and the RPM arm. If not, a qualitative analysis will be carried out identifying any patient anatomy- and treatment planning-related points of interest.

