### Objectives {7}

The primary objective of the study is to test the accuracy and usability of Breathe Well to assist DIBH during breast cancer radiotherapy. Breathe Well will be tested against the commercially available real-time position management (RPM) / respiratory gating for scanners (RGSC) system (Varian Medical Systems, Palo Alto, CA), which has been extended in-house to provide a screen for visual feedback.

The primary hypothesis is that the accuracy of Breathe Well in maintaining the position of the chest during DIBH is superior to the RPM/RGSC system. Because Breathe Well monitors the chest directly, while the RPM/RGSC system uses a marker block positioned on the upper abdomen, Breathe Well has the advantage of utilising a more immediate surrogate of the chest wall position. In addition, we hypothesise that Breathe Well is more user-friendly as it was specifically designed for guiding breast cancer patients through DIBH treatments.

Secondary objectives:To measure the setup times for both the Breathe Well and the modified RPM/RGSC system for all fractions. We hypothesise that Breathe Well can be set up faster than the modified RPM/RGSC system.To investigate patient comfort and user friendliness of Breathe Well via a patient survey (Supplementary Materials). We hypothesise that the patient comfort and usability of Breathe Well is superior to the Varian RPM system.To investigate staff perception of Breathe Well via a technology assessment survey (Supplementary Materials). We hypothesise that the staff perception of Breathe Well is superior to the Varian RPM/RGSC system.To develop — offline — the use of the electronic portal imaging device (EPID) for real-time MLC tracking during monitoring the chest wall position in breast radiotherapy.To investigate, using dose reconstruction, the estimated dose delivered during radiotherapy and compare this with the planned dose.

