### Sample size {14}

The sample size was estimated by assuming that the systematic error in treatment accuracy, Σ, will be smaller for patients on the experimental (Breathe Well) arm than the control (RPM) arm. Previously published data for a different surface monitoring system (AlignRT: VisionRT, London, UK) is given by Kanphet et al. [14] who found a systematic error of 0.46 mm in the vertical direction. For comparison, Lutz et al. [15] found a systematic error of 1.33 mm with RPM. Assuming this study will recruit a comparable patient cohort, that any differences in treatment technique will not affect the target motion, and assuming normal distribution of the systematic error in both arms of the trial and independence of the two arms, the F-test for equality of two variances estimates 36 patients will be needed for statistical significance with a power of 0.8 and alpha error probability of 0.05. The sample size for this study was set at 40 to account for an estimated 10% dropout rate for patients who cannot maintain a breath hold and are treated with free breathing.

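### The dose rule makes the estimate, and not only the superiority claim, conditional on a positive primary result, so a non-positive primary leaves no modelled dose difference or interval

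*Protocol article*

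**What the plan says.** Item 5 of the section Statistical methods for primary and secondary outcomes {20a} sets a two-branch rule for the estimated delivered dose. The first branch reads: "If the primary outcome shows superiority of the Breathe Well arm in treatment accuracy, the same model will be used to test for superiority", here of the dose results. The model meant is the one named for the primary outcome: "a generalized estimating equation model with exchangeable correlation structure which adjusts for repeated measurements within individuals". The second branch reads: "If not, a qualitative analysis will be carried out identifying any patient anatomy- and treatment planning-related points of interest".

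Two other sections describe the dose work without any condition. Objectives {7} lists: "To investigate, using dose reconstruction, the estimated dose delivered during radiotherapy and compare this with the planned dose". Outcomes {12} says that the measured chest wall displacement "will be used to apply an isocentre shift in the treatment planning system", and continues: "Hence the delivered dose will be estimated for each patient during each treatment fraction and aggregated for each arm of the trial".

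**The concern.** Testing a secondary outcome only after a positive primary is a reason to withhold a claim. It is not a reason to withhold an estimate. Item 5 does both, because the between-arm model exists only in the first branch. The second branch covers every result short of superiority, including one that favours the control system. It replaces the model with an unstructured review and names no summary statistic, whereas items 1 to 3 of the same section each promise a median and range.

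Reduced cardiac dose is the reason the protocol gives for breath-hold treatment, and the article says that the findings should help other centres choose a technology. If the primary is not positive, those centres would want to know whether a dose difference of practical size has been excluded. The plan would have the reconstructed doses to address this but no planned estimate or interval.

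There is also a selection element. Dose is computed from the displacements that decide the primary result, so it is modelled only when those displacements favoured Breathe Well.

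**Working it through.** **1. The sections side by side.**

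| Section | Dose work | Conditional on the primary? |
|---|---|---|
| Objectives {7} | delivered against planned dose | no |
| Outcomes {12} | dose per patient and fraction, summarised by arm | no |
| Statistical methods {20a}, item 5 | between-arm model and test | yes |
| Statistical methods {20a}, item 5 | qualitative review | only if the primary is not positive |

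The data for the model exist in both branches, so feasibility does not explain the switch.

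**2. Inputs.** The plan gives no figure for the dose comparison, so there is none to reproduce. Sample size {14} states: "the F-test for equality of two variances estimates 36 patients will be needed for statistical significance with a power of 0.8". The significance level there is 0.05, and its sidedness is not given. With 1:1 allocation, 36 patients are 18 per arm, and 36/0.9 = 40 recovers the recruited total. The power of 0.8 is for a comparison of variances, not for the generalized estimating equation that decides the branch. The effect sizes and correlations below are assumptions.

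**3. Chance of the qualitative branch.** Treat each patient's mean as one observation. With standardised effect d, the expected test statistic is m = d/√(2/n), and the chance of a non-positive primary is Φ(c − m).

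- d = 0.5, n = 18: m = 0.5/0.333 = 1.5. One-sided 0.05: Φ(1.645 − 1.5) = 0.56. Two-sided 0.05: Φ(1.96 − 1.5) = 0.68.
- d = 0.9, n = 18: m = 0.9/0.333 = 2.7. One-sided: Φ(1.645 − 2.7) = 0.15. Two-sided: Φ(1.96 − 2.7) = 0.23.
- If the stated power of 0.8 applied to the primary test: 1 − 0.8 = 0.20.

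**4. Error rate of the dose claim.** In a simulation of 400,000 trials with no true dose effect, a primary effect of 0.5 and primary–dose correlation from 0 to 0.95, the chance of a dose claim was 0.022 to 0.050 at one-sided 0.05. At two-sided 0.05, where the favourable tail is 0.025, it was 0.008 to 0.025. The gate does not inflate the type I error.

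**5. Selection after a positive primary.** With correlation ρ between the two statistics and the same standardised effect on both, the expected dose statistic given a positive primary is m + ρ·φ(c − m)/[1 − Φ(c − m)].

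- d = 0.5, ρ = 0.8, one-sided: 1.5 + 0.8 × 0.395/0.442 = 2.21, and 2.21 × 0.333 = 0.74.
- The same, two-sided: 1.5 + 0.8 × 0.359/0.323 = 2.39, and 2.39 × 0.333 = 0.80.

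Both compare with a true 0.5. In relative terms, with c = 1.96, m = 1.96 + z(power) and ρ from 0.6 to 0.95:

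| Assumed primary power | Average exaggeration |
|---|---|
| 80% | 7.5% to 11.9% |
| 50% | 24.4% to 38.7% |
| 30% | 48.4% to 76.7% |

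The protocol supplies neither ρ nor the power of the primary test, and with ρ = 0 there is no exaggeration.

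**6. What changes if the model is always fitted.** After a positive primary, the same model on the same data gives the same estimate, so the figures in step 5 do not move. After a non-positive primary, an estimate and interval appear where none was planned. On the footing of step 3, the 95% half-width would be about 1.96 × 0.333 = 0.65 standard deviations. That is wide, but it tells the reader what is and is not excluded.

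**The case against.** The case for the plan has real force. Item 5 is prespecified fixed-sequence testing, and step 4 shows that it protects the error rate. Outcomes {12} promises dose figures by arm with no condition. A reader might infer from item 5 that a non-positive primary yields no quantitative dose information at all; the document does not support that, because descriptive arm-level figures remain planned.

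A reader might also infer that the dose objective would go unmet. That goes too far, because Objectives {7} compares delivered with planned dose, not one arm with the other.

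A third tempting reading is that the exaggeration in step 5 measures the harm of the rule. It does not: the percentages rest on assumed correlations, effects and powers, and the estimate after a positive primary is the same with or without the change. That the qualitative branch would lead to selective reporting is likewise conjecture, since it is announced in advance and supports no inferential claim.

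Finally, the article is a condensed account, and the choice of dose metric belongs in the statistical analysis plan. That is fair. But the two-branch rule is a stated rule, not an omitted detail, and it names a qualitative review as what happens after a non-positive primary. Arm summaries without an interval do not answer whether a meaningful difference has been excluded. That part of the concern stands.

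**Conclusion.** The point holds in a limited form. Item 5 makes estimation as well as testing of the between-arm dose difference depend on the primary result, although the dose reconstruction is unconditional. After a non-positive primary there is no planned modelled difference and no interval.

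The chance of reaching that branch cannot be read from the document. It is 20% if the stated power carries over to the primary test, about 15% to 23% with an assumed standardised effect of 0.9 and 18 per arm, and about 56% to 68% with an effect of 0.5. Dose and displacement share their source data, so some positive correlation is to be expected and a dose effect modelled only after a favourable primary will tend to be exaggerated; by how much is not determinable here.

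Type I error and the primary conclusion are unaffected. This is a nearly free improvement to one secondary outcome, not a flaw that threatens the trial.

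**What to change.** Replace the two-branch rule in item 5 with wording to this effect: the dose model will be fitted whatever the primary result, and the between-arm difference in the dose-difference measure will be reported with a 95% confidence interval; superiority in dose will be claimed only if the primary outcome shows superiority; the qualitative review of anatomy and planning will supplement the model in both cases. The scalar dose measure entered in the model can be left to the statistical analysis plan.

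The cost is one or two sentences. No further patients, images or dose reconstructions are needed, and the error control for the dose claim stays as it is. The change brings item 5 into line with the unconditional dose work in Outcomes {12}. It does not remove the selection effect from an estimate that follows a positive primary, and the report should not suggest that it does.
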